## Randomisation

Randomisation will occur at the service level. Enrolled health services will be randomised into Group A and Group B. Randomisation and allocation will be undertaken after six months of providing PSN for all enrolled health service sites and prior to commencement of the training program. All enrolled health service sites will be listed, and a statistician will be responsible for randomizing the health service sites into cluster one (Group A participants) or cluster two (Group B participants) using a block size through a computer program for randomisation.

For the intervention assignment; a cluster crossover randomised trial will be employed in this study, as all participants receive the same intervention based on random service site allocation. Participants in the study sites will know which group they have been allocated after completing six months of the PSN, and before commencing the E-Learning module for group A. The project research team will not be blinded to group A or B allocation, only people analyzing the results will be masked/blinded.

**Peer Support Network (months 1-17):** Only AHW/Ps will participate in the PSN. AHW/P participants from both Group A and Group B will participate in the PSN for the entire duration of the study. The PSN will commence and convene for 6 months prior to Group A doing the e-learning modules and the OS. The PSN will run online via Teams, once a month, for 1.5 to 2 hours duration, and will be facilitated by a credentialed diabetes educator (DNE) who is a research team member.

As this is a pragmatic trial, it is understood that AHW/Ps may not be able to attend all PSN sessions due to competing work and/or personal priorities.

The PSN meetings will not be recorded. The PSN Facilitator will record participation in the network.

**E-Learning Modules (10 weeks):** There are 9 self-paced e-Learning modules. Each module takes approximately 1 hour to complete. Ten weeks have been allocated to complete the e-learning modules. All participants will do the e-learning modules. Services will have agreed to allow their staff to use the work computers and internet and to do the modules during work hours. These can also be done from any computer, at any time. The modules can be left and picked up at the same place for convenience during working hours.

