### **Enabling and supporting on-going connection among the cohort**

A Microsoft Teams site will be created by the research team, who will manage the site so that only the research team can invite and remove members. All participants will be invited to the site. It will house diabetes-related resources approved by the study investigators or the Facilitators of the PSN and OS. One folder within the Teams site will be private only for PSN members. This folder will house the PSN materials. The research team and members will be able to post chats on the site to keep in contact. The chats will not be used as data in the study. The site will be administered and monitored by the research team predominantly the PSN Facilitator, OS Facilitator and Study Manager. On completion of the study, participants will be invited to keep the resources and the Teams site will be deleted by the research team.

During the training intervention a weekly email will go out to participants doing the training program to remind and keep participants moving through the modules (Attachment 11).

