### **On-going communication**

A Friday update in the form of an email will be sent to participants (Attachment 12). This will include the status of the study in the form of a traffic light system and a highlight for the week which will be sourced from a reputable source such as Diabetes Australia, NDSS, RACGP. Each week we will introduce a research team member or a member of the diabetes health profession community including the Investigator team.

An e-newsletter will be produced every 2-months introducing the study, the study investigators, the research team, updates on project progress, links to diabetes resources, diabetes studies and showcasing diabetes organisations will be developed by the research team. It will be distributed to each site through the site representative on the study Steering Committee and to all participants, study investigators and key stakeholders. This will be an important form of communication during the intervention and post intervention. The Principal Researcher, [name] will be responsible for signing off on the Friday update and the e-newsletter.

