## **Data collection timepoints for the primary outcomes**

For the entire study there are seven points in time at which data will be collected. These are labelled T0 (baseline), T1 – T6 in Figure 4 and are referred to in the below outline of data collected. Reason for the training program data collection timepoints are as follows:

- T0- Baseline - groups A & B
- T1 - Measure Effect of Peer Support Network - 6 Months Post Baseline Group A & B (Aboriginal Health Workers and Practitioners only).
- T2 – Measure effect of training program (PSN, Online Modules, Onsite Support) on group A - 8.5 Months post-baseline (data collected on both group A & B).
- T3 – Baseline of group B prior to doing the intervention (data collected on both group A & B), 14.5 months post-baseline.
- T4 – Measure effect of training program (PSN, Online Modules, Onsite Support) on group B post group B undertaking the intervention at 17 months from baseline (data collected on both group A & B).
- T5 – Sustainability of effect of training program on group A 23 months post-baseline, and group B 6 months post commencement of intervention.
- T6 - Sustainability of effect of training program on group A 29 months post-baseline, and group B 12 months post commencement of intervention.

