#### **Primary outcomes**

Directed Acyclic Graphs (DAGs) are being used to determine variables that need to be collected to adjust for potential confounding within statistical models. DAGs enable the conceptualisation of causal pathways. A DAG has been done for each primary outcome.

Generalized linear mixed effects models (GLMMs) with compound symmetric (exchangeable) correlation structure will be used to account for within health care centre (cluster) correlation; logit or log link will be used for binary outcomes such as prevalence resulting in mixed effect logistic regression, while log link will be used for count outcomes resulting in mixed effects negative binomial regression. GLMMs are a missing data method only assuming missing at random – MAR (instead of the more stringent MCAR – missing

completely at random). Effect measures will also be presented through calculation of number needed to treat and its associated 95% confidence interval. Analysis after the 12-month intervention follow-up is planned, spending  $\alpha=0.005$ .

In addition, a descriptive pre-post analysis of survey results due to participating in the PSN alone in the first six months will be calculated using appropriate parametric or non-parametric tests. These analyses will occur after each collection timepoint.

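### The T0–T1 change in Aboriginal Health Workers and Practitioners is tested and credited to the Peer Support Network alone, but the design has no PSN-free group of these staff to support that attribution

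*Protocol*

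**What the plan says.** After the mixed-model analysis, section 11.a (Primary outcomes) adds "a descriptive pre-post analysis of survey results due to participating in the PSN alone in the first six months", which "will be calculated using appropriate parametric or non-parametric tests". It names no comparator. Section 10.c (Data collection timepoints for the primary outcomes) gives the purpose and population of the six-month survey: "T1 - Measure Effect of Peer Support Network - 6 Months Post Baseline Group A & B (Aboriginal Health Workers and Practitioners only").

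Section 10.b (Randomisation) sets the exposure. "Only AHW/Ps will participate in the PSN", and "AHW/P participants from both Group A and Group B will participate in the PSN for the entire duration of the study". The PSN starts in month 1. Services are randomised after six months of it and before Group A starts the modules and onsite support.

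On who answers at T1, the protocol gives two accounts. Section 10.c limits T1 to AHW/Ps. Table 3 lists every primary-outcome instrument at T0 to T6 for all participants, and Table 2 gives multidisciplinary providers seven surveys, the same number as AHW/Ps.

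**The concern.** The stated question is what the PSN does to knowledge, attitude, confidence, practice and skill. A single-group before-after test asks whether the mean score moved between T0 and T1 for any reason. The two questions coincide only if nothing but the PSN can move the scores.

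The protocol itself supplies other possible causes. The same people answer the same instruments twice. Section 10.b also describes a Teams site open to all participants ("It will house diabetes-related resources approved by the study investigators or the Facilitators of the PSN and OS"), a weekly email ("A Friday update in the form of an email will be sent to participants (Attachment 12")) and a two-monthly newsletter with links to diabetes resources. Section 14 says the e-learning modules are already free online.

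This is the only analysis of the primary outcomes assigned to the PSN by itself, and the PSN is one of three programme components. As worded, the trial could report that the PSN improved these outcomes when it had no effect.

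**Working it through.** **Step 1: is there any contrast for the PSN among AHW/Ps?**

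| Feature | Protocol | Consequence for T0–T1 |
|---|---|---|
| PSN exposure | All AHW/Ps, both groups, from month 1 | No unexposed AHW/P |
| Randomisation | After six months of PSN | No randomised contrast in the window |
| Groups A and B | Both keep the PSN throughout | A versus B cannot isolate the PSN later either |
| Instruments | Same scales at T0 and T1 | Retest gain is included in the change |

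The attribution to the PSN alone therefore fails on the design. No outside figure is needed for this.

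**Step 2: the protocol's own size figure.** The Sample section gives uptake of 40, drop-out of 50% and 20 completers. 20 / (1 − 0.5) = 40, so the arithmetic reproduces. I use 20 and 40 only as plausible sizes. The 20 are training completers, not T1 respondents, and the text does not clearly say that all 40 are AHW/Ps.

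**Step 3: how often would the test signal an effect if the PSN had none?** Assumptions not in the protocol:
- non-PSN gain g of 0 to 0.3 baseline SD
- T0–T1 correlation r of 0.5 to 0.7
- two-sided alpha of 0.05 (the only alpha stated, 0.005, belongs to the analysis after 12-month follow-up)
- no clustering.

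The SD of change is √(2(1 − r)) baseline SDs: 1.000 at r = 0.5 and 0.775 at r = 0.7. The standardised drift is d = g / √(2(1 − r)). Rejection follows a noncentral t with n − 1 degrees of freedom and noncentrality d√n. For example, with g = 0.3, r = 0.7 and n = 20: d = 0.3 / 0.775 = 0.387, noncentrality = 0.387 × √20 = 1.73, and the rejection probability is 0.376.

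| Non-PSN gain | n = 20, r 0.5 to 0.7 | n = 40, r 0.5 to 0.7 |
|---|---|---|
| 0 | 0.050 | 0.050 |
| 0.1 SD | 0.071 to 0.085 | 0.095 to 0.125 |
| 0.2 SD | 0.136 to 0.195 | 0.235 to 0.357 |
| 0.3 SD | 0.247 to 0.376 | 0.457 to 0.666 |

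The rate equals 5% only when the non-PSN gain is exactly zero, and for any other gain it rises with sample size.

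**Step 4: would multidisciplinary staff serve as a control?** If they had exactly the same drift, a two-sample t test on change would hold its level: 20,000 simulated trials with a common gain of 0.3 SD of change gave 0.053 (20 v 20) and 0.050 (40 v 20). That result follows from the equal-drift assumption. If drift differs by 0.2 SD between the professions and the PSN does nothing, noncentral t with 2n − 2 degrees of freedom and noncentrality d√(n/2) gives:
- 20 v 20: 0.095 to 0.125
- 40 v 40: 0.143 to 0.207.

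**The case against.** The best defence is that the analysis is introduced as an addition to the main model and is called descriptive. The aim and hypothesis concern the whole programme, and the word alone can be read as meaning before modules and onsite support begin. It stands that this is supplementary and that no randomised conclusion depends on it. The label does not cure the problem, however: tests are planned, the change is described as being due to the PSN, and section 10.c repeats the causal purpose without the word descriptive.

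A reader might infer more than the documents support, in four ways:

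- **That other study resources certainly reached participants before T1.** The Teams site, Friday update and newsletter have no start date, and the newsletter is described as important during and after the intervention. Exposure in months 1 to 6 is possible, and likely for Teams because the PSN runs on it, but it is not established. Retesting and secular change are enough for the point.
- **That this is the only evaluation of the PSN.** A PSN satisfaction survey is a listed secondary outcome, and facilitators keep journals.
- **That the rates above estimate this trial's error.** They depend wholly on an assumed drift.
- **That multidisciplinary staff are a ready control.** Section 10.c says that T1 is for AHW/Ps only, so their data may not exist. Their retest gain may differ from that of AHW/Ps, and because they work in the same services they may learn from PSN members.

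**Conclusion.** The concern holds as a fault of attribution. Sections 10.c and 11.a claim an effect of the PSN from a tested single-group change, and the design contains no AHW/P without the PSN. That part rests on the protocol's text alone.

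The size is illustrative. With zero PSN effect, other gain of 0.2 to 0.3 SD, correlation 0.5 to 0.7 and a two-sided 5% test, false attribution occurs in 14–38% of trials at n = 20 and 24–67% at n = 40. With no other gain it is 5%. The point limits what may be concluded about the PSN component. It does not touch the Group A versus Group B comparison.

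**What to change.** 1. In section 11.a, delete the words attributing the change to the PSN alone. Report within-AHW/P change over the first six months with a 95% confidence interval that allows for clustering by service, with no hypothesis test and no causal claim.
2. In section 10.c, reword the purpose of T1 to match, as a survey of change over the first six months.
3. Reconcile section 10.c (T1 in AHW/Ps only) with Tables 2 and 3 (seven surveys, all participants).
4. Optional, and only if T1 is collected from everyone: add an exploratory comparison of T0–T1 change between AHW/Ps and multidisciplinary staff. Label it non-randomised and state that it depends on equal drift in the two groups. If T0 is an outcome in that model, do not also adjust for it.

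Items 1 to 3 cost protocol wording and, for item 1, a cluster-adjusted interval. They need no new data unless item 3 is settled by extending T1 beyond what is being collected. Item 4 adds one model and should not replace item 1.

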## **Secondary Outcomes**

Provision of evidence-based care and patient biomedical outcomes will be summarised using counts, means and percentages and differences between time collection points reported. Patients will be stratified by for example, age, gender, diabetes type and existing comorbidities.

### **b. Qualitative**

The qualitative data from the study will be analysed using a data-driven, inductive, thematic analysis based on the Braun and Clarke's guide for thematic analysis. Inductive analysis is a process of data coding without fitting it into any pre-existing coding framework. The majority of qualitative data for the study will come from the interviews. The interview transcripts will be audio recorded and transcribed verbatim. The analysis will begin by the analyst repeatedly reading and re-reading the data to become familiar with it. The more formal coding will start once the analyst becomes familiarised with the data. Once the data has been coded, these codes will be sorted into potential themes and subthemes. Once the themes are reviewed, refined, and finalised they will be used to write the final report. We will aim to analyse and report the data separately for AHW and multi-disciplinary team. Combining all disciplines, we will aim to analyse the data by metro and remote.

### **b. De-identification**

Data will be collected at several points in time.

**Individual level data – training program participants:** On entry into the study each participant will be allocated a unique ID (URID) within RedCap. The Study Manager will enter enrolled participant details into RedCap including participant first name, surname, date of birth, email address, enrolment date, consent status, consent status and consent form. This will create a participant list and will assign each participant a URID within RedCap, so that their baseline and subsequent evaluations can be linked for the duration of the study. REDCap keeps the URID, and participant name separate to the participant data. The participant data will only include the URID. Only de-identified data will be analysed during the study. Individual data will not become part of any report or publication of the project.

Data collected by semi-structured interviews with AHW/Ps and multidisciplinary health care providers will not be linked to the survey data. This data will be aggregated and thematically analysed. Name or date of birth will not be collected from interview participants.

**Service level data (systems assessment):** Each health service will be given a unique ID by the Study Manager. A linking key that holds the service name and unique service ID will be kept in a separate file location. All service level information will include the unique ID only.

**Quality of care and patient outcomes (medical record review):** The health service will allocate a unique ID to each patient record, and this will be kept by the service. Only de-identified audit data will be provided to the research team (Attachment 14). Should the research team need to clarify anything, they will provide the relevant health service with the unique ID number; the health service will then follow-up the query using the patient record.

## **12. DATA HANDLING AND RECORD KEEPING**

### **a. Data collection and management responsibilities**

Data collection is the responsibility of the research staff of Wardliparingga Aboriginal Health Equity, SAHMRI, under the supervision of the Principal Investigator. The Data Manager will oversee data management under supervision of the Principal Investigator. The Principal Investigator is responsible for ensuring the accuracy, completeness, legibility, and timeliness of the data reported. The SAHMRI IT department has the expertise and resources to support the management of research data to levels required by external data custodians and as outlined in the National Statement.

Electronic data will be stored on servers protected by firewalls, security groups and passwords. Data will be stored on the secure S Drive. Accessing the S Drive requires a two-step authentication process that comprises of a SAHMRI log in and then individual access to the S Drive folder arranged by the SAHMRI IT. SAHMRI IT requires evidence of ethics approval for those individuals who request access to the study folder located on S Drive.

Data are protected in accordance with the data management policies of Wardliparingga Aboriginal Health Equity, SAHMRI.

### **b. Study records retention**

All data will be saved in electronic format on password-protected computers in a locked office of Aboriginal Health Equity, [name], SAHMRI. On S Drive one master folder will be created that will hold two folders for: 1) individual level data demographics, primary outcomes, potential confounding and peer support network evaluation variables and enablers and barrier to participation, sustainability and effectiveness, and 2) service level data quality and outcomes of diabetes care and service characteristics.

RedCap is an electronic data capture program that will be used to capture most data in this project. RedCap sits on a secure server in Australia that is managed and controlled by SAHMRI. The RedCap unique ID and participant name is stored separately to the participant data which will only record the unique ID. Only the unique ID can be seen and extracted by the research team.

Hardcopy data will be scanned and saved on the S Drive. Audio-transcriptions will be saved on the S Drive.

The Principal Investigator is responsible for retaining data. All data will be stored for 7 years, after which time it will be destroyed in accordance with SAHMRI policy and procedures. Hardcopy data will be destroyed once this is completed at the first opportunity after data collection. Once semi-structured interview data has been transcribed, the audio recording will be destroyed.

### 13. PUBLICATION & INTELLECTUAL PROPERTY

Data from participating Aboriginal primary health care services and individual multidisciplinary health care providers will remain theirs to own, protect, and control. Interview transcripts will be provided to individual participants to review and to keep, should they wish to. System assessment and analysed audit data will be provided to the individual health service that it belongs to. Only aggregated data will be used to generate study outputs. Wardliparingga Aboriginal Health Equity, SAHMRI, will own the Intellectual Property from the study.

Publication of study findings will include:

- Health service reports and presentations
- Key stakeholder information sheets that provide the study findings
- Conference presentations
- Peer reviewed journal publications describing results from each stage

A knowledge exchange and translation plan will be developed with the Steering Committee.

#### a. Dissemination of results to participants

**Training program evaluation:** Where able, participating AHW/Ps and Aboriginal primary care health services will receive results as they are produced.

**Peer Support Network:** Each month, aggregated results of the survey evaluation will be provided to the Peers Support Network and used to improve the Network.

**Systems assessment:** Each service will receive their systems assessment within 3 months of it being completed.

Results will be disseminated via email or via the Teams site in the case of the Peers Support Network evaluation and communicated through the Steering Committee.

Key stakeholders will be provided study results, they include National Association of Aboriginal and Torres Strait Islander Health Workers and Practitioners, Diabetes Australia and their state and territory affiliate members, the National Association of Diabetes Centres, Australian Diabetes Educator Association and the National Aboriginal Community Controlled Health Organisation (NACCHO). As host of the e-learning modules, Diabetes Queensland will be provided aggregated results (only those published) of the evaluations built into the e-Learning modules to inform continual improvements of the e-Learning modules.

**Medical record review:** Each health service will be offered aggregated analysed service level data on patients of their service only. All services in the study will receive combined aggregated results of the audits as they become available.

## **14. ETHICAL CONSIDERATIONS**

The aim is that participants will receive direct benefit from doing the training program in the form of increased knowledge, confidence, skill, practice and attitude towards managing diabetes. Aboriginal Health Workers and Practitioners will benefit from being involved in the Peer Support Network through increased collegial support, sharing information and experiences, and having access to a diabetes nurse education facilitator. All health professionals involved will have access to the e-learning modules for free, they are currently available now for free, hosted on the Diabetes Queensland website. On completion all participants will receive 10 continuing professional development points and a certificate. Participants will also have access to a diabetes educator who will facilitate the onsite support. Only employees within services that allow their staff to participate and use the service internet, computer and clinic site are invited to participate. Benefit to clients with regards to improved quality of care and care outcomes will be evaluated, however the study will not interact with clients, and has requested a waiver to access their diabetes related data to measure potential changes in outcomes.

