### **Informed consent process**

Participation in the Study is voluntary. Several options to ensure potential participants have sufficient information and adequate understanding of the proposed research and the implications for participation will be made available, as follows:

- Participant information sheet
- Presentations on the study by the research team that may be attended by one or more staff from the same service
- Individual phone conversation about what it would mean to participate in the study in the way of purpose, method, demands, risks and potential benefits

With each of these options, potential participants will be invited to have a conversation with a member individually about what participation requires and an opportunity to ask questions.

It will be made clear in all options that not participating will not affect their relationship with their employer or the study team or involvement in future research. A reason for not participating is not required.

It will also be made clear that:

- That the service they are employed by is supportive of the study and has agreed to participation during paid working hours, access to a computer and the internet, on-site support being provided at the service.
- Participants will not be reimbursed for their time spent undertaking the training program
- Data collection is required to evaluate the Diabetes Training Program. We will cover what data will be collected, when including how often, the length of time data collection will take and the format for data collection (e.g., REDCap Survey).
- At any time participants may withdraw from the study without any penalty. The data they have provided can be withdrawn if they wish or can continue to be used in the study with their consent.

Potential participants themselves will have the ability to provide informed consent, no other person or statutory body is required to decide on their participation in the study.

As the methods of the study are pre-defined, full disclosure of the study protocol will be given.

**Training program:** A member of the research team will meet with each potential participant (either in person or via phone or video call) to explain the details of the study, review the Participant Information Sheet (Attachment 4), and provide the AHW/P or multidisciplinary health care providers an opportunity to ask the researcher any questions. If potential

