**Onsite Support (minimum of twice over 10-week period):** The OS sessions will occur during the same 10-week period as the e-Learning modules. The OS will be face to face at the primary health care service. The number of OS sessions and what is covered during them will be negotiated between the participants and the OS Facilitator. It is suggested that each service hold a minimum of 2 sessions with the OS Facilitator. OS sessions will be held as a group, if there is more than one AHW/P or multidisciplinary health care providers within the health service. The group sessions will be held with AHW/Ps for the first half of the session and then include multidisciplinary health care providers for the remainder of the session. This format will be assessed and adapted as needed. This format responds to direct feedback during the co-design of the training program.

The OS will be facilitated by a credentialed diabetes educator (CDE) employed by Diabetes SA. The CDE will be a member of the research team.

**Group A:** At the start of month 7, AHW/P and multidisciplinary health care provider participants within the health services randomised to Group A will commence the e-Learning modules and OS, for a duration of 10 weeks. During this time, AHW/Ps from both Group A and Group B will continue to participate in the PSN.

**Wash out period (6 months):** There is a six month 'wash out' period where only the PSN is running. This will occur between Group A and Group B doing the e-Learning modules and participating in the OS.

**Group B:** After the 6-month washout period the participating AHW/Ps and multidisciplinary health care providers within the health services randomised to Group B will commence the e-Learning modules and OS, for a duration of 10 weeks. During this time, AHW/Ps from both Group A and Group B will continue to participate in the PSN.

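### Group B can take the free public e-learning modules before its month-14.5 start, and the protocol text neither asks it to wait nor names an item recording early use, so the T2 and T3 contrasts can be diluted by an unmeasured amount

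*Protocol*

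**What the plan says.** The study randomises services to Group A or Group B. Group A does the e-learning modules and Onsite Support from month 7. Group B does them after a six-month wash-out in which only the Peer Support Network (PSN) is meant to run (section 10.b). Under the data collection timepoints for the primary outcomes, both groups are measured at T2 (8.5 months), T3 (14.5 months, described as Group B's baseline) and T4 (17 months, after Group B's training).

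On access to the modules:
- Section 14: "All health professionals involved will have access to the e-learning modules for free, they are currently available now for free".
- Section 10.b, E-Learning Modules: "These can also be done from any computer, at any time".
- The description of the intervention in the Background section prints the web link to the modules.
- The consent section says: "As the methods of the study are pre-defined, full disclosure of the study protocol will be given".

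Participants learn their group after six months of the PSN and before Group A starts the modules (Randomisation). Section 14 adds that completion earns professional development points and a certificate.

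On recording exposure, section 10.b says that the PSN Facilitator will record participation in the network. Table 3 lists no item on module use and schedules demographics at T0, T5 and T6 only. It also lists five potential confounding variables with varied timing. Three of these come from the demographic and PSN surveys, and the other two are not named. The full variable list is in Attachment 14.

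**The concern.** Group B is the control only while it has not had the training. Between learning its allocation and its own start it waits 14.5 - 6 = 8.5 months for a course that it can open on any day, with a certificate at the end. Nothing in the protocol text asks it to wait.

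Group B members who complete the modules early and benefit from them are trained people analysed, correctly, as controls. That pulls the T2 and T3 differences towards zero. It also raises the T3 score that serves as Group B's own baseline, so the T3 to T4 change would be understated too. If early use is not measured, a small or null difference cannot be attributed: the programme may not work, or part of the control group may already have had it. A later analysis plan cannot adjust for an exposure that was never collected, so this is a question of trial conduct and survey content.

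**Working it through.** **1. Which timepoints carry the contrast.** The protocol's timeline adds up: 6 + 2.5 = 8.5 months (T2), 8.5 + 6 = 14.5 months (T3), 14.5 + 2.5 = 17 months (T4).

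| Timepoint | Group A modules and Onsite Support | Group B modules and Onsite Support (intended) |
|---|---|---|
| T0, T1 | not yet | not yet |
| T2, T3 | done | not yet |
| T4 to T6 | done | done |

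Only T2 and T3 compare trained with untrained services.

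**2. The plan's own numbers.** The Sample section expects an uptake of 40 with 50% drop-out, leaving 20 who complete: 20 / (1 - 0.5) = 40, which reproduces. It contains no allowance for early use of the modules. With an even split (an assumption, since clusters may be unequal and recruitment has no upper limit), there are 40 / 2 = 20 enrolled or 20 / 2 = 10 completers per group.

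**3. Dilution.** Let p be the fraction of Group B that gains the full module benefit before the measurement. The module part of the contrast becomes (1-p) times its true size.

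- One early user: 1/20 = 5% (enrolled) or 1/10 = 10% (completers).
- Three early users: 3/20 = 15% or 3/10 = 30%.

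The enrolled denominator is the more natural one at T2 and T3, because Group B has not yet begun training and completion is not yet defined for it. The completer figure is the upper end.

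**4. What that would do to sample size and power.** The protocol gives no effect size, variance or rate of early use, so this is illustrative. If the modules carried the whole effect, the required N would rise by 1/(1-p)². A comparison with 80% power at p = 0 would have power Φ[(z + 0.842)(1-p) - z], where z is the two-sided critical value. This is a normal approximation without clustering. The 0.05 level is an assumption; 0.005 is the level that the protocol gives for its analysis after the 12-month follow-up.

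| p (assumed) | Contrast left | N factor | Power, alpha 0.05 | Power, alpha 0.005 |
|---|---|---|---|---|
| 0 | 100% | 1.00 | 80.0% | 80.0% |
| 10% | 90% | 1.23 | 71.3% | 68.3% |
| 20% | 80% | 1.56 | 61.1% | 54.5% |
| 30% | 70% | 2.04 | 50.0% | 40.0% |
| 50% | 50% | 4.00 | 28.8% | 16.3% |

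These are upper limits on the damage for a given p. Onsite Support is also in the contrast. If the modules account for a share s of the total effect and effects add, the total shrinks only to 1 - s·p. With s = 0.5 and p = 20%, that is 1 - 0.10 = 90%, the same as the 10% row.

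**5. Is early use recorded?** The text names PSN participation as recorded and names nothing for the modules. Multidisciplinary providers are not in the PSN, so PSN records could not show their early use. Whether Attachment 14 or the two unnamed confounders fill the gap cannot be settled from the protocol text.

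**The case against.** The strongest reply is that absence from the text is not absence from the plan. Attachment 14 holds the full variable list. The information sheet, collaborative agreement and communication plan (Attachments 4, 10 and 11) are where a request to defer would normally sit. None was available, and this objection stands. It limits the point to what the protocol text names, and the fix is conditional for that reason.

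A reader might go further in several ways that the documents do not support:

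- **That dilution would be undetectable.** Section 13.a mentions evaluations built into the modules, and section 14 mentions a completion certificate. Either might reveal early completion. Group B's own scores at T2 and T3 might also hint at it, although for AHW/Ps a gain could not be separated from a PSN effect. The protocol does not plan to use any of these for this purpose, so unmeasured is fair and undetectable is not.
- **That Onsite Support leaks to Group B.** Of the Teams site the protocol says "All participants will be invited to the site", and that "It will house diabetes-related resources approved by the study investigators or the Facilitators of the PSN and OS". These are general resources, not Onsite Support materials. The only private folder is set by PSN membership ("One folder within the Teams site will be private only for PSN members"), but the support itself stays out of reach: "The OS will be face to face at the primary health care service".
- **That the shared PSN contaminates the control group.** It is the intended background for AHW/Ps in both groups throughout.
- **That feeding back results trains Group B.** The commitment that "participating AHW/Ps and Aboriginal primary care health services will receive results as they are produced" is qualified by the words 'Where able', and seeing aggregate results does not deliver the modules.
- **That module use before randomisation biases the comparison between groups.** Services are randomised afterwards, so such use is balanced in expectation.

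It can also be said that p is assumed and that a sensitivity analysis may sit in an analysis plan. Both are true, but the exposure data must be collected first.

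**Conclusion.** The point holds in a limited form. Group B has unrestricted access to the public modules before month 14.5 and knows its allocation from about month 6. The protocol text neither asks it to wait nor names an item recording early use. The module part of the T2 and T3 contrasts can therefore be diluted by an unmeasured amount: about 5% per early user with 20 enrolled per group, 10% with 10 completers per group.

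This rests on an even split between groups and on early users gaining the full module benefit. Without that gain the dilution is smaller or absent. The protocol gives no rate of early use, so the finding is that dilution is possible and not planned for, not that it will occur. It should be corrected because it affects the only randomised trained-versus-untrained comparisons and exposure left unrecorded is hard to recover later.

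**What to change.** 1. Check Attachment 14. Unless it already has one, add a single dated item to the T0, T1, T2 and T3 surveys, for everyone who receives each survey: has the participant started or completed the diabetes e-learning modules, which ones, and when? Dated completion records from the module host would serve instead. Answers at T0 and T1 separate use before allocation from use after it.
2. Keep the primary analysis as allocated, and pre-specify a sensitivity analysis that accounts for Group B module exposure before T3.
3. Unless Attachment 4, 10 or 11 already does so, ask Group B in the allocation notice to leave the modules until its start date.

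The cost is one survey item, one line in a notice and a voluntary delay for Group B. The Teams site and the feedback of results to services need not change on account of this point.
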